#### **9.4 Treatment Compliance**

Subjects should bring all the IPs and containers when visiting the study site during the study. The number of returned IPs will be checked at each visit, and the dose taken will be recorded by checking the number of drugs actually taken. If a subject's dose taken does not correspond with the number of returned IPs, the reason should be recorded. The overall treatment compliance during the treatment period should be  $\geq 80\%$ , and subjects with treatment compliance of  $< 80\%$  or  $> 120\%$  will be excluded from the Per Protocol Set (PP Set).

$$\text{Treatment compliance (\%)} = \frac{\text{Number of drugs actually taken}}{\text{Number of drugs to be taken during the relevant period}} \times 100$$

## 10 Study Procedures and Assessments

### 10.1 Visit Schedule and Study Schedule Table

#### 1) Visit 1: Screening (from Weeks -9 to -5)

- ① Informed consent and SN assignment:  
Patients selected as potential subjects will be provided with the study-related information through the subject information sheet, and, if they agree, they will provide informed consent by writing down their name, signature, and date as a subject.  
An SN will be assigned in the order of informed consent in the form of a 5-digit number. The first 2 digits will represent the site number and the rest 3 digits will represent the order of informed consent.  
For example, the 5th subject to provide informed consent at site number 8 will be assigned 'SN08-005'.
- ② Demographic information and height:  
Demographic information (including risk group assessment) such as initials, age, and gender will be examined and height (in cm; rounded to one decimal place) will be measured.
- ③ Medical history and treatment history, and concomitant medications:  
Medical history (past medical history, surgical history, and current medical history) within 1 year and all concomitant medications within 4 weeks from the date of informed consent will be examined.
- ④ Vital signs: blood pressure and pulse rate
- ⑤ Physical examination and body weight  
Head, neck, heart, lung, abdomen, liver, skin, extremities, etc. will be examined and body weight (in kg; rounded to one decimal place) will be measured.
- ⑥ Pregnancy test  
A pregnancy test (urine hCG) will be performed only for women of childbearing potential who are not postmenopausal (who have been amenorrheic for at least 12 months) or are not surgically sterile, and appropriate contraceptive methods will be used throughout the study.
- ⑦ Laboratory tests – using central lab  
Subjects should have laboratory tests in a fasting state (fasting for at least 9 hours) to exclude food effect. Subjects who are not in a fasting state should revisit to have the laboratory tests.

| Laboratory tests      | Items                                                                                                                                                                     |
|-----------------------|---------------------------------------------------------------------------------------------------------------------------------------------------------------------------|
| Hematology            | WBC with differential count (neutrophil, lymphocyte, monocyte, eosinophil, basophil), RBC, Hb, Hct, platelet                                                              |
| Blood chemistry       | Ca, P, glucose, HbA1c, BUN, uric acid, creatinine, total protein, albumin, total bilirubin, direct bilirubin, AST, ALT, ALP, LDH, $\gamma$ -GT (GGT), CPK (CK), Na, K, Cl |
| Urinalysis            | Specific gravity, PH, protein (albumin), glucose, ketone, occult blood, urobilinogen, nitrite                                                                             |
| Thyroid function test | TSH, free T4                                                                                                                                                              |
| Lipid parameters      | LDL-C, HDL-C, TG, total cholesterol, Apo-A1, Apo-B, non-HDL-C/HDL-C ratio, total cholesterol/HDL-C ratio, LDL-C/HDL-C ratio, Apo-B/Apo-A1 ratio                           |

\* One re-test is allowed.

- ⑧ Electrocardiography (ECG) - will be performed if deemed necessary by the investigator.  
12-lead ECG will be used.
  - ⑨ Assessment of inclusion/exclusion criteria and discontinuation of lipid lowering agents  
Subjects determined eligible will stop using current antihyperlipidemic agents.
  - ⑩ Training on TLC:  
Subjects will be trained on TLC for the treatment of hypercholesterolemia during the study.
- #### 2) Visit 2: Run-in period (Week -1)
- \*If drug-naïve subjects or subjects who have not taken fibrates for  $\geq 8$  weeks or agents other than fibrates for  $\geq 4$  weeks at screening meet the inclusion/exclusion criteria without a wash out period, Visit 2 will be skipped.
- ① Vital signs  
Blood pressure and pulse rate will be measured.

- ② Physical examination and body weight  
Head, neck, heart, lung, abdomen, liver, skin, extremities, etc. will be examined and body weight (in kg; rounded to one decimal place) will be measured.
  - ③ Pregnancy test  
A pregnancy test (urine hCG) will be performed only for women of childbearing potential who are not postmenopausal (who have been amenorrheic for at least 12 months) or are not surgically sterile, and appropriate contraceptive methods will be used throughout the study.
  - ④ Laboratory tests – using central lab  
Subjects should have laboratory tests in a fasting state (fasting for at least 9 hours) to exclude food effect. Subjects who are not in a fasting state should revisit to have the laboratory tests.  
\* One re-test is allowed. If a re-test is performed, the run-in period may last until Week -2 (Day -14).
  - ⑤ Assessment of AEs and concomitant medications  
AEs that occurred and concomitant medications taken since last visit will be examined.
  - ⑥ Training on TLC:  
Subjects will be checked if they have been implementing TLC for the treatment of hypercholesterolemia since last visit.
  - ⑦ Discontinuation of lipid lowering agents  
Subjects will continue to stop using antihyperlipidemic agents.
  - ⑧ Assessment of inclusion/exclusion criteria
- 3) Visit 3: Treatment period (Week 0)**
- ① Pregnancy test  
A pregnancy test (urine hCG) will be performed only for women of childbearing potential who are not postmenopausal (who have been amenorrheic for at least 12 months) or are not surgically sterile, and appropriate contraceptive methods will be used throughout the study.  
\* At Visit 3, pregnancy will be verified immediately using a pregnancy test kit provided by the central lab and the result will be recorded in the source document.
  - ② AN assignment  
Subjects who finally meet the inclusion/exclusion criteria will be randomized by the IWRS. An AN is a 5-digit number, and the first 2 digits will represent the site number and the rest 3 digits will represent the order of randomization.  
For example, the 5th subject to be assigned an AN at site number 8 will be assigned 'AN08-005'.
  - ③ Dispensing of IPs  
The IPs to be taken for 12 weeks (doses for 100 days with overage for 16 days included) will be dispensed, and subjects will be recommended to take 1 tablet of the IP once daily at the same time of the day and will take the drug starting from the day of dispensing. Subjects will be instructed not to take the IP on the day of the next visit (Visit 4), and if they took the IP, they should revisit to have the scheduled tests. Subjects will be instructed to bring unused IPs when visiting the site.
  - ④ Assessment of AEs and concomitant medications  
AEs that occurred and concomitant medications taken since last visit will be examined.
  - ⑤ Training on TLC:  
Subjects will be checked if they have been implementing TLC for the treatment of hypercholesterolemia since last visit.
- 4) Visit 4: End of study visit (Week 12)**
- ① Vital signs  
Blood pressure and pulse rate will be measured.
  - ② Physical examination and body weight  
Head, neck, heart, lung, abdomen, liver, skin, extremities, etc. will be examined and body weight (in kg; rounded to one decimal place) will be measured.
  - ③ Pregnancy test  
A pregnancy test (urine hCG) will be performed only for women of childbearing potential who are not postmenopausal (who have been amenorrheic for at least 12 months) or are not surgically sterile, and appropriate contraceptive methods will be used throughout the study.
  - ④ Laboratory tests – using central lab

Subjects should have laboratory tests in a fasting state (fasting for at least 9 hours) to exclude food effect. Subjects who are not in a fasting state should revisit to have the laboratory tests.

- ⑤ ECG - will be performed if deemed necessary by the investigator.  
12-lead ECG will be used.
  - ⑥ Collection of returned drugs and assessment of treatment compliance  
The IPs dispensed to the subjects at Visit 3 will be collected and treatment compliance will be assessed.
  - ⑦ Assessment of AEs and concomitant medications  
AEs that occurred and concomitant medications taken since last visit will be examined.
  - ⑧ Training on TLC:  
Subjects will be checked if they have been implementing TLC for the treatment of hypercholesterolemia since last visit.
- 5) Unscheduled Visit**  
During the study, subjects may visit the study site and have necessary tests, if necessary (i.e., when an AE occurs or is suspected). The investigator will remind the subjects about this at regular visits and instruct them to contact the investigator immediately if an AE occurs. Unscheduled visits will be recorded on the e-CRF.

## **10.2 Efficacy Endpoints and Assessments**

### **10.2.1 Primary Efficacy Endpoint**

Percent change from baseline in LDL-C at Week 12

### **10.2.2 Secondary Efficacy Endpoints**

- 1) Percent changes from baseline in lipid parameters at Week 12  
\* Lipid parameters: HDL-C, TG, total cholesterol, Apo-A1, Apo-B, non-HDL-C/HDL-C ratio, total cholesterol/HDL-C ratio, LDL-C/HDL-C ratio, Apo-B/Apo-A1 ratio
- 2) Changes from baseline in HbA1c and glucose at Week 12
- 3) Percentage of subjects achieving the target LDL-C by risk group
- 4) Percentage of subjects achieving the target non-HDL-C by risk group

### **10.2.3 Exploratory Endpoint**

Average cost effectiveness ratio (ACER) for LDL-C at Week 12 from baseline

## **10.3 Safety Endpoints and Assessments**

### **10.3.1 Adverse Event**

- 1) Incidence of AEs, adverse drug reactions (ADRs), serious adverse events (SAEs), and serious adverse drug reactions (SADRs) that occur throughout the study
- 2) Incidence of unexpected AEs, ADRs, SAEs, and SADRs

### **10.3.2 Vital signs**

Vital signs results assessed by visit time point

### **10.3.3 Laboratory tests**

Percentage of clinically significant abnormal laboratory results

## **10.4 Adverse Event Reporting**

### **10.4.1 Definitions**

- 1) An “adverse event (AE)” refers to any unfavorable and unintended sign (including abnormal laboratory test results), symptom, or disease in a subject who received the IP which does not necessarily have to have a causal relationship with the IP.
- 2) An “adverse drug reaction (ADR)” refers to any unfavorable and unintended response to the IP of any dose, for which causal relationship to the IP cannot be ruled out.
- 3) A “serious adverse event/adverse drug reaction (SAE/SADR)” refers to an AE or an ADR at any dose of the IP that:
  - A. Results in death or is life-threatening
  - B. Requires or prolongs hospitalization  
However, hospitalization due to the following reasons is not considered as an SAE:
    - Hospitalization or prolongation of hospitalization for planned surgeries for diagnoses or existing diseases
    - Hospitalization or prolongation of hospitalization required to measure the effect of the study
    - Hospitalization or prolongation of hospitalization for planned treatment of the studied indication
    - Emergency room visit for less than 24 hours
    - Hospitalization for health examination
  - C. Results in persistent or significant disability/incapacity
  - D. Results in congenital anomalies or birth defects
  - E. Important medical events such as the development of drug dependency or drug abuse or blood dyscrasia

- 4) An “unexpected adverse drug reaction” is any reaction of which the nature or severity of the reaction is not consistent with the available product-related information including the Investigator’s Brochure or the package insert of the product.

#### 10.4.2 Recording of Adverse Events

It is the principal investigator’s and study staff’s responsibility to record all AEs occurring in the study. AEs should be recorded in medical diagnostic terms, and if this is not possible, they should be recorded using the terms for signs and symptoms observed by the principal investigator or the study staff, or reported by subjects.

#### 10.4.3 Assessment of Severity

Severity of AEs will be determined by the principal investigator or the study staff based on their clinical judgment. It will be based on the maximal intensity and can be classified by the criteria below.

| Grade | Description                                                                                                          |
|-------|----------------------------------------------------------------------------------------------------------------------|
| 1     | Mild
No special treatment required.
Abnormal laboratory test or radiography results, etc. without any symptoms |
| 2     | Moderate
Simple, local, or non-invasive treatment, etc.                                                           |
| 3     | Severe
Hospitalization or invasive treatment such as transfusion, therapeutic endoscopy, or surgery required      |

#### 10.4.4 Assessment of Causal Relationship to the Drug

The correlation between the administration of the IP and onset of the event will be determined by the principal investigator or the study staff based on their clinical judgment. The criteria for assessment of causal relationship to the IP will be classified as below in accordance with Annex 4-3. Post-marketing Safety Control Standards for Medicinal Products, etc. of the Regulation on the Safety of Pharmaceuticals, etc., and all events except ones assessed as “Unlikely” will be considered to have causal relationship to the IP. Also, for events assessed as “Unlikely”, the basis of the decision will be recorded on the e-CRF.

| Causal relationship |                             | Basis of decision                                                                                                                                                                                                                                                                                                  |
|---------------------|-----------------------------|--------------------------------------------------------------------------------------------------------------------------------------------------------------------------------------------------------------------------------------------------------------------------------------------------------------------|
| 1                   | Certain                     | The AE follows a reasonable temporal sequence from administration of the IP, not explained by other drugs, chemicals, or accompanying diseases, follows a clinically reasonable response on withdrawal, and is pharmacologically or phenomenologically decisive when such drug, etc. was re-administered as needed |
| 2                   | Probable/Likely             | The AE follows a reasonable temporal sequence from administration of the IP, not explained by other drugs, chemicals, or accompanying diseases, follows a clinically reasonable response on withdrawal (no re-administration information)                                                                          |
| 3                   | Possible                    | The AE follows a reasonable temporal sequence from administration of the IP, but it is also explained by other drugs, chemicals, or accompanying diseases. Also, information about the drug discontinuation is insufficient or unclear                                                                             |
| 4                   | Unlikely                    | It is only a temporary case that does not seem to have a causal relationship with administration of the IP, and it can also be explained by other drugs, chemicals, or accompanying diseases                                                                                                                       |
| 5                   | Conditional/Unclassified    | For appropriate evaluation, more information is required, or additional data are under review                                                                                                                                                                                                                      |
| 6                   | Unassessable/Unclassifiable | A judgment cannot be made because the information is insufficient or contradictory, and the information cannot be supplemented or verified.                                                                                                                                                                        |
| 7                   | Not applicable              |                                                                                                                                                                                                                                                                                                                    |

#### 10.4.5 Actions Taken for Adverse Events

##### 1) Action taken with the IP

| No. | Classification   |
|-----|------------------|
| 1   | Dose increased   |
| 2   | Dose not changed |
| 3   | Dose reduced     |

|   |                |
|---|----------------|
| 4 | Drug withdrawn |
| 5 | Unknown        |
| 6 | Not applicable |

## 2) Other actions

| No. | Classification                                      |
|-----|-----------------------------------------------------|
| 1   | Concomitant administration of treatment medications |
| 2   | Non-medication treatment                            |
| 3   | Not applicable                                      |
| 4   | Unknown                                             |

## 10.4.6 Outcome of Adverse Events

| No. | Classification                        |
|-----|---------------------------------------|
| 1   | Recovered                             |
| 2   | Recovering                            |
| 3   | Not recovered                         |
| 4   | Recovered with sequelae               |
| 5   | Fatal injury                          |
| 6   | Unknown                               |
| 7   | Death possibly correlated with the AE |
| 8   | Death unrelated to the AE             |

## 10.4.7 Reporting of Serious Adverse Events/Adverse Drug Reactions

During this study, the principal investigator and the study staff should ensure the safety of subjects and minimize AEs by taking an appropriate measure promptly in the event of any SAEs.

If an SAE occurs during the study, the obligations of each staff member are as follows.

### 1) Obligations of the principal investigator

If an SAE occurs during the study, it must be reported to the Institutional Review Board (IRB) in accordance with the standard operating procedures (SOP) of the IRB at each study site. The principal investigator or the study staff must report it to Chong Kun Dang Pharmaceutical Corp. within 24 hours or no later than the next business day, regardless of its relationship to the IP. If necessary, a further report including detailed information should be submitted within 7 days to the PV team of Chong Kun Dang Pharmaceutical Corp.

- [contact]
- [contact]
- Address: [name]
- E-mail address of the PV responsible person at Chong Kun Dang Pharmaceutical Corp.:  
[contact]

### 2) Obligations of the study staff

The study staff must report to the principal investigator immediately if an SAE occurs during the study.

### 3) Obligations of the sponsor

The sponsor must report all AEs that occur during the study to the investigators, the IRB, and the president of Korea Institute of Drug Safety & Risk Management within the following timeframes.

- ① SADRs: within 15 days from the sponsor's receipt of the report or awareness of the event
- ② All SAEs that do not constitute ①: within 1 month from the end of each quarter
- ③ All AEs that do not constitute ① and ②: within 1 month from the end of the quarter where clinical study report submission is due

## 10.4.8 Follow-Up of Adverse Events

The principal investigator or the study staff should follow the subjects with AEs until the symptoms subside and the abnormal laboratory test results return to the reference value, or a satisfactory explanation for the observed changes is provided. In addition, they should report on the course of the AEs to the staff in charge at Chong Kun Dang Pharmaceutical Corp.

## 10.4.9 Pregnancy during the Study

Pregnancy during the study will not be considered as an AE, and hospitalization for an elective abortion (excluding

therapeutic abortion) without any complications or normal live birth of a healthy newborn will not be considered as an SAE.

If a subject (or a spouse/partner) becomes pregnant during the study (from the first dose of the IP to 28 days after the last dose), a pregnancy report should be prepared and submitted to the sponsor within 24 hours of becoming aware of the pregnancy.

To collect pregnancy information, however, the patient's signature on the informed consent form for collection of pregnancy information should be obtained first. If a subject becomes pregnant, administration of the study drug will be discontinued immediately, and the subject will be withdrawn from the study.

Even if the subject discontinues participation in the study or is terminated from the study, the sponsor should follow up on and document the progress of pregnancy for both mother and baby until birth.

## 11 Data Analysis and Statistical Considerations

### 11.1 Analysis Sets

#### 11.1.1 Full Analysis Set (FAS)

The full analysis set (FAS) means an analysis set that includes all randomized subjects in the analysis and is closest and fully applicable to the intention-to-treat (ITT) principle. Therefore, the FAS will include the subjects that receive at least one dose of the IP after randomization in this study and have at least one efficacy assessment after the IP administration.

#### 11.1.2 Per Protocol Set (PP Set)

The per protocol set (PP Set) will exclude the following subjects considered to have committed a major protocol deviation from the randomized set.

- 1) Subjects who are terminated from the study early before the protocol-specific time point
- 2) Subjects who are considered to have committed a major protocol deviation
- 3) Subjects with overall treatment compliance of < 80% or > 120%

#### 11.1.3 Safety Analysis Set

The safety analysis set will include subjects who are randomized in this study and take at least one dose of the IP after its receipt.

### 11.2 Statistical Analysis Method

#### 11.2.1 General Principles of Analysis

All statistical analyses in this study will be performed with a two-sided test at a significance level of 5%. If any missing value is found in the efficacy data, the efficacy analysis will be performed applying the last observation carried forward (LOCF), and the analysis of the safety data will be performed using raw data without applying the LOCF.

#### 11.2.2 Demographic Information and Other Pre-Treatment Characteristics

The subject's demographic information and pre-treatment characteristics of the IP will be summarized and analyzed by treatment group for the FA set. For continuous data such as age, descriptive statistics (mean, standard deviation, median, minimum, and maximum) will be presented and the independent samples t-test will be performed for comparison between the treatment groups. For categorical data such as gender and age group, the number and percentage (%) of subjects will be presented and the chi-square test or the Fisher's exact test will be performed for comparison between the treatment groups.

Concomitant medications will be classified into prior medications (administration started before the IP administration) and concomitant medications (administration started after the IP administration) and coded using the WHO-ATC Index. The number and percentage (%) of subjects by 1st level of the WHO-ATC Index will be presented, and the chi-square test or the Fisher's exact test will be performed for comparison between the groups.

In addition, medical history will be coded using MedDRA version 20.0. The number and percentage (%) of subjects by System Organ Class (SOC) will be presented, and the chi-square test or the Fisher's exact test will be performed for comparison between the groups.

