| Statistical Analysis | 
 
▶ General Principles of Analysis
All statistical analyses in this study will be performed with a two-sided test at a significance level of 5%. If any missing value is found in the efficacy data, the efficacy analysis will be performed applying the last observation carried forward (LOCF), and the analysis of the safety data will be performed using raw data without applying the LOCF.
 
▶ Demographic Information and Other Pre-Treatment Characteristics
The subject's demographic information and pre-treatment characteristics of the IP will be summarized and analyzed by treatment group for the full analysis set (FA Set). For continuous data such as age, descriptive statistics (mean, standard deviation, median, minimum, and maximum) will be presented and the independent samples t-test will be performed for comparison between the treatment groups. For categorical data such as gender and age group, the number and percentage (%) of subjects will be presented and the chi-square test or the Fisher's exact test will be performed for comparison between the treatment groups.

Concomitant medications will be classified into prior medications (administration started before the IP administration) and concomitant medications (administration started after the IP administration) and coded using the WHO-ATC Index. The number and percentage (%) of subjects by 1st level of the WHO-ATC Index will be presented, and the chi-square test or the Fisher's exact test will be performed for comparison between the groups.

In addition, medical history will be coded using MedDRA version 20.0. The number and percentage (%) of subjects by System Organ Class (SOC) will be presented, and the chi-square test or the Fisher's exact test will be performed for comparison between the groups.
 
▶ Analysis of the Efficacy Endpoints
The efficacy endpoints will be analyzed with the FA Set as the primary analysis set and the Per Protocol Set (PP Set) as the secondary analysis set.               
 
1. Primary efficacy endpoint
The mean percent change from baseline in LDL-C at Week 12 will be compared between the study group and the control group, and to demonstrate that LDL-C lowering effect in the study group is superior to that in the control group, the independent samples t-test or the Wilcoxon rank sum test will be performed.
 
2. Secondary efficacy endpoints                   
 
1) The mean percent changes from baseline in lipid parameters at Week 12 will be compared between the study group and the control group using the independent samples t-test or the Wilcoxon rank sum test.
 
 
 
 
* Lipid parameters: HDL-C, TG, total cholesterol, Apo-A1, Apo-B, non-HDL-C/HDL-C ratio, total cholesterol/HDL-C ratio, LDL-C/HDL-C ratio, Apo-B/Apo-A1 ratio
 
 
 |

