#### 2) Drugs that increase the frequency of side effects or cause abnormal plasma concentration when used concomitantly

- ① CYP3A4 inhibitors (cyclosporine, macrolide antibiotics, azole antifungals, and protease inhibitors): erythromycin, atazanavir, clarithromycin, indinavir, itraconazole, ketoconazole, nefazodone, telaprevir, tipranovir+ritonavir combination, lopinavir+ritonavir combination, saquinavir+ritonavir combination, fosamprenavir, darunavir+ritonavir combination, fosamprenavir+ritonavir combination, etc.
- ② Drugs that affect thyroid function (administration of anti-thyroid agents or thyroxine: subjects on replacement therapy are not applicable)
- ③ CYP3A4 inducers: rifampin, carbamazepine, efavirenz, etc.
- ④ P-glycoprotein inhibitors: cyclosporine, verapamil, and diltiazem
- ⑤ Colestipol
- ⑥ Oral contraceptives containing norethisterone and ethinyl estradiol
- ⑦ Antacids
- ⑧ Grapefruit juice: intake of 1.2 L or more per day is not allowed
- ⑨ Nicotinic acid
- ⑩ Gemfibrozil

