#### 3) Other investigational agents

If criteria for temporary or stable use for each agent are met, the following drugs may be used concomitantly. For temporary use, a short-term use within 7 days is allowed, but they must not be taken or administered within 4 days

prior to a scheduled visit. For stable use, they may be taken or administered as long as their dosage is not changed from the time of informed consent until the end of the study.

- Drugs allowed for temporary use: systemic steroids and antacids
- Drugs allowed for stable use: P-glycoprotein inhibitors, oral contraceptives, antacids, and drugs that affect thyroid function (administration of anti-thyroid agents or thyroxin: subjects on replacement therapy are not applicable)

Subjects who sign the informed consent form should be trained to follow guidelines on TLC for the treatment of hypercholesterolemia, as much as possible.

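### The start-date rule labels every drug ongoing at first dose as prior, so neither medication table shows on-treatment exposure by arm

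*Protocol*

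**What the plan says.** Section 11.2.2 gives the rule: "Concomitant medications will be classified into prior medications (administration started before the IP administration) and concomitant medications (administration started after the IP administration"). The statistical part of the synopsis repeats it: "prior medications (administration started before the IP administration) and concomitant medications (administration started after the IP administration"). Neither place uses a stop date or an ongoing status, and there is no class for a drug started earlier and continued into treatment.

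Section 11.2.2 then adds: "The number and percentage (%) of subjects by 1 st level of the WHO-ATC Index will be presented", with a chi-square or Fisher's exact test between groups. Nothing limits the counts or tests to one of the two classes.

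Section 9.3 decides which otherwise prohibited drugs may be used alongside the IP. One list reads "Drugs allowed for stable use: P-glycoprotein inhibitors, oral contraceptives, antacids, and drugs that affect thyroid function", on the condition that they are used "as long as their dosage is not changed from the time of informed consent until the end of the study". A second list reads "Drugs allowed for temporary use: systemic steroids and antacids", for short courses. All four stable-use classes also appear under the section 9.3 heading "Drugs that increase the frequency of side effects or cause abnormal plasma concentration when used concomitantly".

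**The concern.** In section 9.3, and in section 9.2 on medications taken during the study, concomitant means taken alongside the IP. In section 11.2.2 it means started after the IP. The two meanings differ exactly for drugs already in use at first dose, and these include the drugs that section 9.3 singles out as interacting but tolerates when the dosage is constant.

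What is at stake is how the results are read. Section 3.1 states an aim of showing no significant difference in adverse-event incidence between the doses, and the trial is open-label. A reader of that comparison will want to know what else subjects were taking during treatment. A table headed concomitant medications would be taken to answer that question, and under this rule it undercounts on-treatment use.

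**Working it through.** The protocol gives no figure for medication use, so the check applies the rule to each kind of use that the protocol foresees.

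**Timing.** Consent is at Visit 1. The first IP dose is on the day of Visit 3. Stable use requires a constant dosage from consent to study end, so compliant stable use must already be running at Visit 1 and must continue through Week 12.

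**Rule applied.**

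| Kind of use | Started | Taken on treatment? | Class under 11.2.2 |
|---|---|---|---|
| Compliant stable use (section 9.3) | before IP | yes | prior |
| Any other permitted drug ongoing at first dose | before IP | yes | prior |
| Lipid-lowering agent stopped at Visit 1 for wash-out | before IP | no | prior |
| Temporary steroid or antacid course begun during treatment | after IP | yes | concomitant |
| Any other drug begun during treatment | after IP | yes | concomitant |

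The first three rows share a label although two are on-treatment use and one is not. The four on-treatment rows are split between the labels. The concomitant class therefore misses ongoing drugs, and the prior class mixes them with stopped ones. Adding the two classes together does not help, because the stopped drugs remain in the sum.

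**Size by definition.** Share of compliant stable use labelled prior: 100%. Share labelled concomitant: 0%.

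**Illustration (assumed counts, not from the protocol).** Let s be the subjects per arm on a stable-use drug and m the other subjects in that arm who start a drug after the IP. The share of on-treatment users missing from the concomitant table is s / (s + m).

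- s = 5, m = 10: 5/15 = 33%
- s = 20, m = 5: 20/25 = 80%
- s = 40, m = 10: 40/50 = 80%
- any s above 0, m = 0: 100%

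Over s from 5 to 40 and m from 0 to 10, the share runs from 33% to 100%.

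**What does not depend on the rule.** The section 11.4 sample size reproduces: 2 × (1.96 + 1.28)² × 13² / (−6)² = 98.56, so 99 per group; 99 / 0.8 = 123.75, so 124 per group and 248 in total. Power with 99 per group is 90.1%. The primary test in section 11.2.3 is an unadjusted t-test or Wilcoxon rank sum test and uses no medication data.

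**The case against.** The strongest reply is that nothing is lost. Section 11.2.2 tabulates and tests both classes, so a stable-use P-glycoprotein inhibitor is still compared between arms, as a prior medication. Drugs running unchanged at first dose are also pre-treatment characteristics, which is the subject of section 11.2.2. Drugs begun after randomisation could be influenced by open-label treatment, so there is a reason to show them separately. Control of interacting drugs rests on the prohibitions and conditions in section 9.3, on checks for prohibited medication at each visit, and on excluding major deviations from the PP Set. No section makes this table the check for imbalance.

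Most of this stands, and it limits the point. A reader might infer that the comparison omits every interacting drug taken during treatment, or that an imbalance could never be seen. The protocol does not support either reading: ongoing drugs are compared under prior, and temporary antacids or steroids begun on treatment are counted as concomitant. Nor does ATC 1st level isolate individual interacting drugs under any definition.

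The reply does not remove the mismatch. A pure baseline class would hold drugs ongoing at first dose, without those already stopped; the prior class holds both. And the label concomitant is used against its meaning in section 9.3.

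**Conclusion.** The point holds as a small misclassification fixed in the protocol text, not as a detail left open for later. All compliant stable use, and any other drug ongoing at first dose, is labelled prior although it is taken during treatment. On-treatment exposure by arm can then be read from neither table.

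The 100% and 0% follow from the definitions and assume only that subjects keep to the stable-use condition. The 33% to 100% range rests on assumed counts and serves only as an illustration.

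It might be tempting to conclude that the LDL-C comparison is confounded or the primary analysis compromised. The documents do not support that: no endpoint, analysis set, significance level, power or sample size depends on this classification. It is a worthwhile correction to a descriptive table that gives context for the safety results.

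**What to change.** In section 11.2.2 and in the statistical part of the synopsis, replace the start-date rule with:

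- *Prior*: stopped before the first IP dose.
- *Concomitant*: taken on or after the first IP dose, whatever the start date, including drugs ongoing at first dose.

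Drugs ongoing at first dose may also be flagged as ongoing at baseline. That keeps them distinguishable from drugs begun after randomisation and preserves the useful part of the present split.

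The cost is one sentence in two places and one programming rule. No visit or clinical procedure changes. Medications are already recorded on the e-CRF and changes are reviewed at every visit. The rule needs start and stop dates or an ongoing status; the protocol does not list the e-CRF fields, so their presence should be confirmed.

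The change makes the concomitant table show what subjects took on treatment. It does not make a table at ATC 1st level able to show individual interacting drugs.
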